## Abstract

**Background:** Artificial intelligence-based software may automatically detect ischaemic stroke lesions and provide an Alberta Stroke Program Early CT score (ASPECTS) on CT, and identify arterial occlusion and provide a collateral score on CTA. Large-scale independent testing will inform clinical use, but is lacking. We aim to test e-ASPECTS and e-CTA (Brainomix, Oxford UK) using CT scans obtained from a range of clinical studies.

**Methods:** Using prospectively collected baseline CT and CTA scans from 10 national/international clinical stroke trials or registries (total >6600 patients), we will select a large clinically representative sample for testing e-ASPECTS and e-CTA compared to previously acquired independent expert human interpretation (reference standard). Our primary aims are to test agreement between software-derived and masked human expert ASPECTS, and the diagnostic accuracy of e-ASPECTS for identifying all causes of stroke symptoms using follow-up imaging and final clinical opinion as diagnostic ground truth. Our secondary aims are to test when and why e-ASPECTS is more or less accurate, or succeeds/fails to produce results, agreement between e-CTA and human expert CTA interpretation, and repeatability of e-ASPECTS/e-CTA results. All testing will be conducted on an intention-to-analyse basis. We will assess agreement between software and expert-human ratings and test the diagnostic accuracy of software.

**Conclusions:** RITeS will provide comprehensive, robust and representative testing of e-ASPECTS and e-CTA against the current gold-standard, expert-human interpretation.

## Introduction

Accurate and rapid identification and quantification of CT imaging features indicative of early ischaemic and haemorrhagic stroke is required to correctly triage patients for urgent treatment. However, early ischaemic brain changes can be subtle on non-enhanced CT (NECT) and identification requires training and experience^1^. The Alberta Stroke Program Early CT Score (ASPECTS) helps quantify early ischaemia on CT and may aid decision making prior to thrombolysis and thrombectomy^2^–^4^. It is particularly important to exclude acute intracranial haemorrhage as the cause of stroke prior to thrombolytic therapy since thrombolysis may worsen haemorrhage. Additionally, a CT angiogram (CTA) may be required immediately after NECT to identify patients with arterial obstruction who are suitable for thrombectomy. Interpretation of CTA also requires training and experience.

A potential solution to help interpret brain CT and CTA after suspected stroke is offered by e-ASPECTS and e-CTA diagnostic software (Brainomix Ltd, Oxford UK). This software, developed using machine learning, includes an automated ASPECTS and detection of acute haemorrhage on NECT, and a CTA assessment to detect large vessel obstruction (LVO) and collateral blood supply. e-ASPECTS is said to be as accurate as expert human rating of ASPECTS^5^,^6^, and the software has been promoted to support and accelerate stroke treatment decisions. However, as is the case with many diagnostic tools developed using machine learning^7^, e-ASPECTS lacks independent demonstration of reliability, safety or clinical utility, especially for newer features of haemorrhage detection and CTA assessment^8^. It is also unclear how e-ASPECTS handles other pathologies which make up around 20% of patients presenting with stroke-like symptoms (i.e. stroke mimics) such as tumours, subdural haematomas or infections.

The Real-world Independent Testing of e-ASPECTS Software (RITeS) study will independently evaluate the accuracy, reliability and clinical benefit of e-ASPECTS and e-CTA software. Here we pre-specify the statistical analysis plan for RITeS.

## Methods

### Study design

We will test the accuracy of e-ASPECTS and e-CTA software for the automated assessment of CT scans performed acutely for suspected stroke among representative patients. We will compare e-ASPECTS/e-CTA with expert human readers who form the current reference standard. We will use CT scans from acute stroke trials that include a range of commonly encountered scan appearances including early ischaemia, haemorrhage, typical pre-stroke features and mimics. All scans have been rated by panels of experts representing many different individuals across these non-commercial trials. We will in addition, perform new human-ratings for a subgroup of the previously collected scans to compare the time needed for human versus e-ASPECTS assessment of CT and to assess the clinical impact of e-ASPECTS software on acute stroke care, i.e. whether it influences diagnostic confidence or alters treatment decisions.

### Patient population

A clinically representative sample (equivalent to the patient population for whom e-ASPECTS or e-CTA may routinely be used) of baseline NECT brain and CTA scans will be selected from the following 10 multicentre national and international randomised-controlled trials (RCTs) and observational studies of stroke: Alteplase versus tenecteplase for thrombolysis after ischaemic stroke (ATTEST)^9^; European multicentre, randomised, phase III clinical trial of therapeutic hypothermia plus best medical treatment versus best medical treatment alone for acute ischaemic stroke (EuroHyp-1)^10^; Third International Stroke Trial (IST-3)^11^; Lothian study of INtraCerebral Haemorrhage Pathology, Imaging and Neurological outcome (LINCHPIN)^12^; Pragmatic Ischaemic Thrombectomy Evaluation (PISTE)^13^; POst-Stroke Hyperglycaemia (POSH)^14^; Penumbra and Recanalisation Acute Computed Tomography in Ischaemic Stroke Evaluation (PRACTISE)^15^; REstart or STop Antithrombotics Randomised Trial (RESTART)^16^; Rapid Intervention with Glyceryl trinitrate in Hypertensive stroke Trial-2 (RIGHT-2)^17^; Safe Implementation of Treatments in Stroke (SITS) open study^18^. These trials collectively include over 6600 individual patients accessible to RITeS; see Table 1 for individual trial numbers and details of available imaging.

All of these trials individually obtained research ethics committee approval. Consent was acquired from or on behalf of all recruited patients.

Baseline CT scans in these trials were scored using very similar methods (often using identical pre-validated schema, i.e. five of the trials used IST-3 methodology for scan assessment^19^, all studies of ischaemic stroke included ASPECTS scoring), and similar patient demographic baseline and outcome data were collected. Scan ratings were obtained by expert readers, nominated by the trials, without knowledge of any clinical baseline or follow-up data, follow-up scans or treatment. Expert rating included assessment for: ASPECTS^2^; acute ischaemia in brain regions other than the MCA territory^1^,^20^; acute intracranial haemorrhage^21^; structural stroke mimics, pre-stroke brain changes (brain atrophy, leukoaraiosis, old stroke lesions)^3^ and image quality. Baseline CTA scans were scored for: arterial obstruction location and extent^22^; collateral extent^23^. 

All of these trials recorded patient demographics (e.g. age, sex), time from stroke onset, included some measure of stroke severity -National Institutes of Health Stroke Scale (NIHSS) for ischaemic stroke, and Glasgow Coma Scale (GCS) for haemorrhagic stroke, and assessed clinical outcome at 90 days or later.

### Inclusion and exclusion criteria

We will derive separate but overlapping samples for e-ASPECTS and e-CTA testing from all baseline scan data available to RITeS. We will produce a STARD-type (Standards for Reporting Diagnostic Accuracy Studies) flow chart^24^ to show reasons for inclusion/exclusion of cases and successful/non-successful scan assessment by human-readers and software for all patients available to RITeS.

**
*Sample for e-ASPECTS evaluation.*
** There are no precise data for the true case-mix of patients initially assessed for presumed stroke, and for whom hospital admission staff may decide to use e-ASPECTS and e-CTA software to assess treatment eligibility. Pooled data from the major thrombolysis and thrombectomy RCTs will be similar to the case-mix considered for these treatments but may include patients with more severe stroke than those seen in routine practice and will not include patients who present late^4^,^25^. Conversely, patients with haemorrhagic stroke are most likely to be severely affected by stroke symptoms^26^, and a proportion may be too sick to be appropriately represented in trials. The Sentinel Stroke National Audit Programme (SSNAP) provides routinely collected UK data for all patients ultimately diagnosed with stroke in England, Wales and Northern Ireland and includes many patients with minor symptoms or delayed/uncertain time of presentation who would not routinely be considered for thrombolysis or thrombectomy^27^. Importantly, all of these data sources only include patients after excluding structural stroke mimics. RIGHT-2 recruited patients at first contact with ambulance staff in the community and reported 26% stroke mimics^17^. A prospective single-centre study of patients with suspected stroke following stroke expert review after arrival at hospital found a similar proportion of mimics^28^. Additionally, in up to 7% of patients with stroke, it is only possible to obtain imaging of poor quality due to patient movement, beam hardening artefacts or variable patient orientation in the scanner, all of which may influence the performance of e-ASPECTS and e-CTA software^3^,^11^. Finally, the sensitivity and specificity of diagnostic tests may vary with prevalence^29^. 

To derive a ‘real-world’ dataset from all patients available to RITeS, and simultaneously maximise sample size, we will therefore: 1) Include all structural stroke mimics for e-ASPECTS testing (since this will be far less than 26%, but see planned sensitivity analyses for our primary outcomes below)2)For the remainder of included patients (i.e. non-mimics), aim for sex and age mix, stroke severity and time since symptom onset similar to SSNAP, pooled thrombolysis/ thrombectomy RCT data, and haemorrhagic stroke registry data.3)Not exclude imaging based on quality.

The most recent SSNAP annual dataset (Apr 2018-Mar 2019) identified 87,635 patients presenting acutely with stroke and had 93% data completion. Of these patients, 47.8% were female, median age was 77 years, 87.1% of strokes were ischaemic, 12.4% were haemorrhagic (0.4% unknown), and the median NIHSS was 5. For 69.4% of patients, the time of symptom onset was known and the median time from stroke onset to baseline scan in these patients was 4 hours and 2 minutes^30^. A pooled analysis of nine thrombolysis RCTs by the Stroke Thrombolysis Trialists’ Collaborative (STTC) group included 6,756 patients of whom 45% were female, the mean age was 71 years, the mean NIHSS was 12, and the mean treatment delay was 4 hours^25^. A pooled analysis of seven thrombectomy RCTs by the Highly Effective Reperfusion evaluated in Multiple Endovascular Stroke Trials (HERMES) collaboration included 1764 patients of whom 47% were female, the median age was 67 years, the median NIHSS was 17, and the mean time from onset to randomisation was 3 hours^4^. A comprehensive, community-based audit of haemorrhagic stroke in Scotland (The Lothian Audit of the Treatment of Cerebral Haemorrhage, LATCH) included 137 patients with primary haemorrhagic stroke of whom 55% were female, the median age was 79 years, and the median Glasgow Coma Scale at presentation was 13^31^,^32^.

To ascertain the representativeness of the non-mimic cases within the RITeS dataset, we will report demographic and clinical data as per SSNAP, STTC, HERMES and LATCH data (see Table 2). We will report absolute differences, 95% confidence intervals and p-values for comparisons. We will also present continuous data components using overlapping histograms.

To ascertain the representativeness of relevant radiological features in RITeS, we will also report the features listed in Table 3.

**
*Sample for e-CTA evaluation.*
** The main indication for acute stroke CTA currently is to determine if the patient is suitable for thrombectomy; such patients are more likely to have a more severe ischaemic stroke and to be younger than the median age of all stroke. CTA is used at some sites prior to thrombolysis but this is not universal and there is no standard or widely agreed practice. There is also less CTA data available in RITeS for testing. We will therefore include all patients for e-CTA testing from all available RITeS trials where CTA was performed routinely at baseline, i.e. we will not select a representative subsample.

### Sample size considerations

Tests of diagnostic accuracy are difficult to power and benefit from maximising the sample size^33^. In addition, sample size calculations may be inappropriate in this setting^34^. We therefore aim for the largest representative sample possible within available resources. However, to allow direct comparison with previous work, we estimated that to confirm that e-ASPECTS software is non-inferior for an “MCC (Matthews Correlation Coefficient) better than random” (to expert human calculation of ASPECTS using an MR diffusion-weighted imaging reference standard: e-ASPECTS correlation 0.44 versus 0.38 for experts), based on 34 patients^35^, requires a sample size of 494 scans – at 5% non-inferiority limit with 80% power and at 5% significance level. Therefore, we have set the minimum sample size for our primary outcome at 500 unique patient CT brain scans. Up to 31% of scans may fail to give an e-ASPECTS result for technical reasons^36^, therefore we will inflate the minimum sample to 725 scans (i.e. 1/0.69 × 500) to ensure the successfully processed sub-sample includes the requisite minimum 500 scans. However, this minimum will have limited power for subgroup analyses (e.g. on pre-stroke brain changes, by age or stroke severity strata) and the study cited for our power calculation used individual ASPECTS regions rather than individual patients to power their analysis, which due to lack of independence between individual ASPECTS regions, may be flawed^35^. Therefore we will process every available scan to derive the largest possible sample for testing.

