We will classify e-ASPECTS and expert-human scores into three groups to assess diagnostic accuracy at the following clinically relevant cut-points, and present a summary (receiver-operating characteristic) ROC curve: 1) ASPECTS 10 (normal) versus ASPECTS 0-9 (abnormal)2) ASPECTS 0-7 versus 8-10^2^.3) ASPECTS 0-5 versus ASPECTS 6-10^4^.

To compare with previous work, we will use Matthews correlation coefficient (MCC), and test non-inferiority between e-ASPECTS and expert-human scores^5^,^35^. We will calculate MCC as (TPxTN)-(FPxFN)/√(TP+FP)(TP+FN)(TN+FP)(TN+FN)^46^. We will set our non-inferiority margin at 5%. Thus using the two one-sided test (TOST) procedure, we will establish non-inferiority, using the following formula: at the α=5% significance level, if the lower limit of a (1-2α) × 100% (i.e. 90%) confidence interval for the difference (e-ASPECTS minus expert-human results) is above -5%. The confidence interval is set at (1-2α) rather than the usual (1-α) because the method is equivalent to performing two one-sided tests^47^,^48^.

**
*2. Accuracy of e-ASPECTS versus expert human readers for identifying cause of stroke symptoms.*
** We will compare the diagnostic accuracy of e-ASPECTS software and expert human readers (at baseline, blind to all other clinical data including further imaging) for three groups against the reference standard, human-expert opinion using all available follow-up data including further imaging: 1) Identifying features of ischaemic stroke (including ischaemic lesions in any brain location and/or intracranial hyperattenuating arteries)2) Identifying haemorrhage, and3) Identifying any structural causes of stroke symptoms on baseline imaging (including mimics).

In addition, to aid clinical understanding and real-world applicability, we will summarise all primary outcome results using normalised frequencies. Thus we will present results as proportions of 1000 individual patients, i.e. a test sensitivity of 90% would be presented as: the test will detect disease in 900 of 1000 patients with the disease, but 100 patients with the disease will be missed by the test^49^.

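### The 494 scans at 80% power match a formula for two independent proportions, so the 80% is not the power of the planned paired MCC comparison

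*SAP article*

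**What the plan says.** Under Sample size considerations, the SAP article estimates that showing non-inferiority for an "MCC (Matthews Correlation Coefficient) better than random" "requires a sample size of 494 scans", "at 5% non-inferiority limit with 80% power and at 5% significance level". The inputs are "e-ASPECTS correlation 0.44 versus 0.38 for experts", "based on 34 patients". It concludes that "we have set the minimum sample size for our primary outcome at 500 unique patient CT brain scans", and inflates this to 725 to allow for up to 31% processing failures.

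The test itself is under Statistical analysis, Primary outcomes, item 1: "We will set our non-inferiority margin at 5"%, with non-inferiority concluded "if the lower limit of a (1-2α) × 100% (i.e. 90%) confidence interval for the difference (e-ASPECTS minus expert-human results) is above -5"%. MCC is defined there from all four cells of the 2×2 table. The same item compares software and expert case by case, on the same scans.

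The sample size section also carries caveats. It says that such calculations may be inappropriate in this setting, that subgroup power is limited, that the cited study's use of regions rather than patients may be flawed, and that every available scan will therefore be processed.

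**The concern.** A power statement belongs to a particular estimator, variance and design. Here the estimator is a difference between two MCCs measured on the same scans. Its variance depends on disease prevalence, on each reader's sensitivity and specificity, and on how often both readers err on the same scan. The plan gives none of these, yet states one N and one power. If the N comes from a formula for a different estimator and design, the 80% says nothing about the planned comparison.

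At stake is the justification for the minimum of 500 successfully processed scans. A reader of the eventual report could take 500 successes as enough for the MCC test, and could misread a failure to show non-inferiority, because the plan claimed 80% power at that size.

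**Working it through.** **Inputs from the plan.** Software 0.44, experts 0.38, so an assumed true difference of +0.06; margin 0.05; power 80%; one-sided 5%, since the test uses the lower limit of a 90% interval.

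**Step 1: reproduce 494.** For two independent proportions:

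n per group = (1.645 + 0.842)² × [0.44×0.56 + 0.38×0.62] / (0.06 + 0.05)² = 6.185 × 0.482 / 0.0121 ≈ 246.4, rounded up to 247.

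2 × 247 = 494, the stated figure. Variants of the same formula miss it:

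- one-sided 2.5%: 626 in total
- a relative 5% margin (0.019): 956
- zero true difference: 2,332 (both 0.38) to 2,438 (both 0.44)

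The inflation is also right: 500/0.69 = 724.6, so 725.

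**Step 2: variance.** The formula implies a standard deviation per observation of √(0.38×0.62) = 0.485 to √(0.44×0.56) = 0.496. In simulation at n = 494, the standard deviation of a single MCC times √n is about 0.91-0.93 at prevalence 0.5, 0.98-1.01 at 0.3 and 1.48 at 0.1. The assumed value is roughly half of the true one, or less. Taken alone, this makes 494 too few.

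**Step 3: pairing.** With both readers on every scan, 494 scans give 494 observations per reader, not 247, and positive correlation between readers shrinks the variance of the difference further. If p(1-p) and the +0.06 are kept, 494 pairs give 97% power at zero correlation and more above it. Taken alone, this makes 494 more than enough.

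**Step 4: both together.** Power = Φ[(0.05 + δ)/SE − 1.645], where δ is the true difference and SE the standard error of the paired MCC difference at n = 494. The plan does not give what is needed for SE, so these are assumptions: prevalence 0.3-0.5, the same specificity for both readers between about 0.7 and 0.95, sensitivity set to give the required MCC, and within-disease error correlation 0-0.6.

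| True difference | SE, worst to best | Power |
|---|---|---|
| +0.06 | about 0.064 to 0.031 | 0.11/0.064 − 1.645 = 0.07, 53%; 0.11/0.031 − 1.645 = 1.90, 97% |
| 0 | about 0.065 to 0.0305 | 0.05/0.065 − 1.645 = −0.88, 19%; 0.05/0.0305 − 1.645 = −0.01, 50% |

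At +0.06 the result turns mainly on error correlation: about 53-72% at correlation 0, all below the claim, and about 85-97% at 0.6, all above it.

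**Step 5: the scans likely to be available.** The ischaemic trials in Table 1 sum to 104 + 98 + 3,035 + 65 + 113 + 271 + 1,149 + 293 = 5,128. After 31% failures, 5,128 × 0.69 ≈ 3,538 remain. At zero true difference, simulated power is then about 66% to over 99% under the same assumptions, before any cases are removed to make the sample representative.

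**The case against.** **The formula is inferred.** This is true. One other route comes close: a paired calculation with the large-sample correlation variance (1−r²)² gives 495 pairs. It needs a correlation of 0.3 between the two estimates, which appears nowhere in the plan, and it still misses by one. The independent-proportions formula is exact using only stated inputs.

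**The assumed advantage is disclosed.** A non-inferiority calculation may assume a non-zero true difference, and the plan shows both values and says that they come from 34 patients. This stands: +0.06 is optimistic, but it is not an error. Power at zero difference is a sensitivity check that the reader needs.

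**The plan already hedges, and little depends on 494.** The minimum is a floor against more than 6,600 patients, MCC is included for comparison with previous work, and diagnostic accuracy statistics are named as the principal method. This limits the consequence. None of the caveats, however, concerns the variance or the pairing, and the text still goes on to set the primary-outcome minimum from the calculation.

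**A corrected power needs inputs the plan lacks.** This is also true. Besides prevalence and error correlation, the plan does not say which reference the experts' own MCC is measured against in the first primary outcome. No single corrected N can be given.

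**Stronger readings.** A reader might infer that the arithmetic is wrong, or that the study is underpowered. The documents support neither: 494 and 725 both reproduce, power at +0.06 can lie on either side of 80%, and the analysed sample should be far larger than 500. Nor can full reassurance be drawn from the 5,128 ischaemic-trial patients, since that count precedes processing failures and representative sampling.

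**Conclusion.** The point holds as one of sample-size method. The 80% attached to 494 scans belongs, on an exact match, to a comparison of two independent proportions. It is not the power of a paired MCC difference, and the floors of 500 and 725 rest on it. The variance fault and the pairing fault pull in opposite directions, so the plan's figure is unsupported rather than shown to be too high or too low. The ranges in the working (53-97% at +0.06, 19-50% at equality) depend on assumed prevalence, specificity and error correlation and would move with them. The practical effect is modest, because every available scan is processed. A correction is worthwhile because the plan uses the figure to set the minimum for a primary outcome.

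**What to change.** Withdraw the 80% power claim for 494/500 scans and replace it with one of the following.

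1. State power for the paired MCC difference at both +0.06 and zero true difference, over a stated range of prevalence, specificity and within-disease error correlation. Use the number of scans expected after up to 31% failures and after representative sampling, and name the reference against which both MCCs are computed.
2. Keep 500 as the minimum but justify it by the width of the confidence intervals for sensitivity and specificity, which Analysis principles and general considerations makes the principal method. As an illustration, prevalence 0.3-0.5 gives 150-250 diseased scans in 500. The widest 95% half-width for sensitivity (at 50%) is then about 1.96 × √(0.25/150) = 8.0 to 1.96 × √(0.25/250) = 6.2 percentage points.

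Either option costs a few lines of text and, for the first, a short simulation. No extra scans are needed.
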